##### Demographics

A demographic survey for all participants (school and CBO) will include age, gender identity, race/ethnicity, education, years of training/terminal degree completion, primary discipline, experience, and work setting/activities performed.

##### Organizational social context (OSC)

The OSC is a measure of general/molar organizational culture and climate [15]. In the current study, only three subscales: Proficiency, Stress and Functionality will be administered; subscale *α* = 0.78–0.94.

##### Implementation Leadership Scale (ILS)

The ILS, a measure of implementation leadership [25, 79], has 12 items loading onto four subscales: Proactive Leadership, Knowledgeable Leadership, Supportive Leadership, and Perseverant Leadership; subscale *α* = 0.95–0.98.

##### Implementation Climate Scale (ICS)

The ICS, a measure of implementation climate [24, 80], includes 18 items loading onto a total score and six subscales: Focus on EBP, Educational Support for EBP, Recognition for EBP, Rewards for EBP, Selection for EBP, and Selection for Openness; subscale *α* = 0.81–0.91.

##### Implementation Citizenship Behavior Scale (ICBS)

The ICBS is a measure of an individual’s implementation citizenship behavior (i.e., the extent to which employees go “above and beyond the call of duty” for EBP implementation) [81] and consists of six items loading onto two subscales: Helping Others and Keeping Informed; subscale *α =* .94–.95 [56].

##### Attitudes toward evidence-based practices scale (EBPAS)

Clinician attitudes toward evidence-based practice will be measured using a version of the EBPAS [82] that was adapted for use with education sector service providers and consists of 16 items that load onto four subscales: Requirements, Appeal, Openness, and Divergence; subscale *α =* .59–.90.

##### Expanded school mental health collaboration instrument (ESCI)

The ESCI [64] will be used to evaluate both clinician embeddedness and mental health service quality. The Outreach and Approach by Mental Health Professionals subscale includes 13 items and assesses the level of embeddedness of community-mental health clinicians in schools. Improvements in school mental health delivery will be assessed with three additional subscales from the ESCI: Support for Teachers and Students (how students and teachers are supported through SBMH programming, 8 items); Increased Mental Health Programming, (improvements in services at school, 5 items); and Improved Access for Students and Families (3 items); subscale *α =* .84–.94.

##### Fidelity/integrity

Consistent with prior organizational research [81], implementation integrity will be evaluated via a modified set of four items completed independently by clinicians and supervisors. Integrity items address practices used with clients, competence, and adherence. Internal consistency for these ratings has been found to be high (*α* = .97) [81]. As final component of this measure, respondents also will provide information about the specific EBP that they have implemented in their work setting.

##### Acceptability and appropriateness

Acceptability and appropriateness of new EBP will be assessed using the four-item Acceptability of Intervention Measure (AIM) and Intervention Appropriateness Measure (IAM) [83], tailored to ask generally about evidence-based practices. The measures have been found to have good inter-item reliability (0.85 for acceptability, 0.91 for appropriateness) and test-retest reliability (0.83 for acceptability, 0.87 for appropriateness).

#### Analyses

Basic data screening procedures will be conducted to screen for errors and explore normality, linearity, form, and outliers. Data will be transformed as appropriate. Statistical analyses will be conducted using commonly available software packages (SPSS [84], Stata [85], Multilevel/Hierarchical Level Modeling [MLM/HLM] [86], and R [87]).

##### Inter-organizational alignment

IOA is the degree to which schools and CBOs exhibit similarity on organizational variables linked to implementation (e.g., general/molar organizational culture; implementation leadership). To describe variability in alignment, we will first use the intra-class correlation coefficient, which estimates variability in each variable that is common across schools and CBOs. Prior research has suggested that difference scores are not ideal as a measure of agreement because they provide no information about whether the effect of a difference depends on the level of either variable [88, 89]. Thus, IOA will be analyzed using polynomial regression with response surface analysis [90, 91] described below.

##### Modeling approach

A multilevel modeling (MLM) framework will allow us to account for the fact that approximately 35 SBMH clinicians in approximately 25–30 schools will be nested within 10–12 CBOs. Because this design will capture nearly all of the school-serving CBOs in two regions, analyses will provide near population level estimates of effects. Thus, analyses will focus on obtaining effect size estimates rather than on traditional hypothesis testing; these estimates will be used to inform the qualitative aims. We will use the estimated effects from these models to guide the development and design of qualitative interview guides addressing organizational factors found to most strongly predict implementation outcomes. We will first estimate the effects of each measure of the organizational implementation context (e.g., general/molar organizational climate, implementation climate) on each implementation outcome, using CBO and school organizational variables as unique predictors of clinician level implementation outcomes. We also will include individual variables (e.g., EBP attitudes) in the multilevel models as level 1 (i.e., clinician level) covariates, testing whether their inclusion improves model fit via likelihood-ratio testing. Next, we will examine the effects of IOA in two ways. First, for each variable, we will model an interaction between CBO and school context; the size of the interaction provides an estimate of the *interdependent* effects of the school and the CBO organizational variables. We also will examine the effects of alignment using the polynomial regression with response surface analysis approach [92], which examines nonlinearity of alignment effects (e.g., effects of alignment when organizational variables are rated similarly in both organizations) and allows a visual examination of the effects of alignment. Finally, we will estimate the effects of our organizational variables on embeddedness for each organization (school or community-based organization) independently, estimate the effects of inter-organizational alignment on embeddedness, and examine the moderating effects of embeddedness on the separate influences of the school and CBO contexts. Overall, this analytic approach will enable us to obtain effect size estimates of the inter-organizational factors that impact clinician implementation outcomes, which will be used as the foundation for the qualitative phase of the project.

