##### Power

Our study is largely focused on estimating effects of an entire population rather than computing statistical significance or generalizing to a larger population and therefore potentially less susceptible to issues associated with calculating effect sizes in small samples [93, 94]. Nevertheless, we calculated power to detect effects in MLM by computing a “corrected sample size,” which adjusts the sample size by the correlation due to nesting [68, 95]. Assuming an ICC of .10 [96], our effective sample size to detect effects on clinician-level implementation outcomes with 35 clinicians would be *n* = 29. Thus, the proposed study has the sensitivity at power (1-*β*) = .80 (*α* = .05) to detect effects as small as *f*^2^ = .37.

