## Discussion

### Innovation

This study will address significant gaps in implementation science knowledge and is innovative by simultaneously examining the organizational contexts of multiple settings (schools and CBOs providing mental health services in schools), linking inter-organizational alignment to implementation, assessing the role of clinician embeddedness, and evaluating the mechanisms through which these processes impact clinician implementation outcomes. Previous implementation research in SBMH has been almost entirely qualitative and has focused on how the organizational factors of *either* the school [111, 112] *or* the CBO [113, 114] individually affect implementation. Notwithstanding the contributions of this research, conducting research in silos does not capture the dynamic and interactive nature of organizations and the influence they have on the delivery of high-quality integrated care. No research has simultaneously examined the unique organizational contexts of both schools and CBOs involved in the implementation of mental health EBP. This neglects the dual administrative relationship that typifies SBMH, where services are most commonly provided by clinicians who are trained and employed outside of the education system [57]. Examining the impact of these organizations simultaneously not only has potential to improve implementation science in SBMH but may be generalizable to other integrated care settings.

Further, contemporary implementation frameworks typically assume a single organization within which system-level processes influence service quality and implementation success. This perspective does not represent the emerging realities of modern mental health care [3, 4] and inhibits what can be learned about organizational processes in implementation. This study is the first to examine the specific impact of IOA in an integrated care setting. Findings have the potential to spur future implementation science that considers the complex relationships across organizations, inform efforts to design and tailor implementation enhancement interventions that attend explicitly to the inter-organizational context, and optimize the capacity of implementation science to guide practice in increasingly complicated systems of care.

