### Limitations

First, the current project is designed to estimate the effects of inter- and intra-organizational variables on implementation outcomes but is not powered for traditional significance testing within a multilevel framework. Recent work shows that studies with less than optimal statistical power can produce important scientific findings and result in more scientific value per dollar spent than larger sample sizes [116]. Further, null hypothesis testing yields less information about the potential reproducibility of study findings than parameter estimates and accompanying confidence intervals [117, 118]. Consequently, we have framed our research questions and design—for both main and moderating effects—in terms of the magnitude, direction, and precision of effect estimates in order to determine the plausibility of effects. There are approximately 13 CBOs operating in the two participating school districts in which we will recruit participants. We intend to include 90–100% of them in the current study, providing an estimate of effects that approximates the population parameters for these regions.

Second, this study is cross-sectional. We considered a longitudinal design that would evaluate changes in organizational constructs (and their alignment) at multiple time points but determined that the limited literature on IOA, objective of estimating effects, and resource limitations were most conducive to a cross-sectional design. Third, although objective indicators of some implementation outcomes (e.g., integrity) may be ideal, objective outcomes that would be common across agencies, schools, and EBP are not available. Instead, subjective and generalizable individual- and team-level EBP implementation outcome measures were drawn from prior research conducted by members of the study team [24, 79]. These measures allow for responses from multiple informants, which have previously been found to overcome some self-report/common method biases [119, 120].

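### The planned 10–12 CBOs meet the stated 90–100% coverage only at 12, and CBO coverage does not make effects from 30–35 clinicians near-population estimates

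*Protocol article*

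**What the plan says.** Under Modeling approach, the protocol article states that "approximately 35 SBMH clinicians in approximately 25–30 schools will be nested within 10–12 CBOs". It continues: "Because this design will capture nearly all of the school-serving CBOs in two regions, analyses will provide near population level estimates of effects". The next sentence draws the consequence: "Thus, analyses will focus on obtaining effect size estimates rather than on traditional hypothesis testing". The same paragraph uses the estimated effects to guide the interview guides toward the strongest predictors of implementation outcomes.

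Under Power, the study is described as mainly concerned with a whole population, and "therefore potentially less susceptible to issues associated with calculating effect sizes in small samples". A conventional calculation follows ("Assuming an ICC of .10"), giving an effective n of 29 from 35 clinicians and a detectable f² of .37 at 80% power and α = .05.

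Under Limitations: "There are approximately 13 CBOs operating in the two participating school districts", and "We intend to include 90–100% of them in the current study". That coverage is then said to give estimates approximating the population parameters for these regions. The same section says that the study is not powered for traditional significance testing and prefers estimates with confidence intervals.

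Participants gives 30–35 clinicians and 90 school personnel. Under Aim 1 Procedures, the school staff are those whom the clinicians identify. Measures asks for at least three ratings per organizational construct.

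**The concern.** Two things do not fit.

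First, the coverage figure behind the near-population argument does not match the number of CBOs in the model over most of its range.

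Second, the argument moves from coverage of one level (CBOs) to a property of estimates made at another (clinicians). Clinician-level effects carry residual variation, error in the organizational ratings, possible non-response, and overfitting when several terms are fitted to about 35 observations. Enumerating the CBOs removes none of these.

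At stake is how the Aim 1 coefficients are read. If they are taken as close to population values, a noisy ranking of predictors could be given more weight than it can bear when the emphasis of the Aim 2 interviews is chosen.

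**Working it through.** **Inputs.** About 13 CBOs and 90–100% intended coverage (Limitations); 10–12 CBOs, about 35 clinicians and 25–30 schools (Modeling approach); ICC .10, effective n 29 and f² .37 (Power); 30–35 clinicians and 90 school personnel (Participants).

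**1. The plan's own figures.** Design effect = 1 + (m − 1) × ICC, with m = 35/k clinicians per CBO for k CBOs. Effective n = 35/design effect.

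| CBOs (k) | Share of 13 | m | Design effect | Effective n |
|---|---|---|---|---|
| 10 | 76.9% | 3.50 | 1.250 | 28.0 |
| 11 | 84.6% | 3.18 | 1.218 | 28.7 |
| 12 | 92.3% | 2.92 | 1.192 | 29.4 |
| 13 | 100% | 2.69 | 1.169 | 29.9 |

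The stated 29 is reproduced with 11 or 12 CBOs. The stated f² of .37 is reproduced at n = 29 if two predictors are tested jointly (noncentral F, λ = f² × n, giving 0.374). The article does not state the number of predictors, so two is an inference. With one predictor the value is 0.29, and with five it is 0.56.

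**2. Coverage.** 0.90 × 13 = 11.7, so 90–100% of 13 means 12 or 13 CBOs. The model's 10–12 gives 77%, 85% or 92%. Only 12 satisfies both statements. Because 13 is approximate, neighbouring values were also tried: a population of 12 gives 83–100%, and a population of 14 gives 71–86%.

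**3. What coverage does for precision.** In the table, with 35 clinicians held fixed, moving from 77% to 100% coverage raises the effective n from 28.0 to 29.9. On the plan's own method, precision is governed by the number of clinicians and hardly by the share of CBOs enrolled.

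**4. Size of the remaining uncertainty.** Fisher-z interval: tanh[atanh(r) ± 1.96/√(n − 3)]. The value r = .30 is an illustration and does not come from the article.
- n = 29: 0.310 ± 1.96/√26 = 0.310 ± 0.384, giving −.07 to .60.
- 30 clinicians in 10 CBOs: m = 3, design effect 1.20, n = 25. Then 0.310 ± 1.96/√22 = 0.310 ± 0.418, giving −.11 to .62.

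**5. Overfitting.** With p terms and no true effect, expected R² = p/(n − 1). A quadratic response surface ordinarily has five terms (two linear, two squared, one product; assumed here). At n = 29 this gives 5/28 = 0.18 by chance alone.

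**6. School side of alignment.** 90 school personnel over 25–30 schools is 3.0–3.6 per school. They are nominated by clinicians, so the school scores rest on a small, selected set of raters.

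**The case against.** The strongest reply is that the article is more careful than a hostile reading suggests. The two CBO ranges meet at 12, the population is only approximately 13, and 90–100% is an intention. The Power section says potentially less susceptible and then gives a conventional calculation. Limitations admits low power and frames results by magnitude, direction and precision. For describing these two regions, high coverage does reduce CBO-level sampling error: the finite-population multiplier √((13 − k)/12) is 0.50, 0.41 and 0.29 for 10, 11 and 12 of 13. All CBO-employed clinicians are also to be recruited from each site.

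Most of this stands, and it limits the severity. It does not rescue the inference. Recruiting all clinicians is not the same as all responding, and no total is given from which clinician or school coverage could be judged. Rater error, residual variation and overfitting would survive full response.

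Four stronger readings are tempting but unsupported:
- **That the counts flatly contradict each other.** They overlap at 12.
- **That a CBO-level effect has only 12 observations' worth of information (−.33 to .75 for r = .30).** With 35 clinicians in 12 CBOs, 35/(1 + 1.92 × ICC) falls to 12 only at ICC = 1; the plan assumes .10.
- **That the article claims its coefficients for a wider population.** The remark that the work "may be generalizable to other integrated care settings" is hedged and conceptual, and Limitations confines the population claim to these regions.
- **That Aim 2 stands or falls with the coefficients.** Under Qualitative interview protocol, feedback reports cover all the organizational constructs measured in Aim 1.

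The degrees-of-freedom method can be left to the analysis plan, and the article proposes no finite-population correction.

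**Conclusion.** The point holds in a limited form. The planned CBO count is 77–92% of about 13 and reaches the stated 90–100% only at 12. Separately, the step from CBO coverage to near-population estimates, and to lower susceptibility to small-sample problems, does not follow. The effects are estimated from 30–35 clinicians with an effective n of about 29, where a moderate observed correlation is compatible with anything from no effect to a large one.

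The interval is a simple correlation approximation, not the planned multilevel estimate. It takes the plan's ICC of .10 as given and an assumed r of .30. The coverage percentages take 13 at face value.

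Severity is moderate (should-fix). The design and the estimation focus can stand, because Limitations already gives a sound reason for them; it is the stated justification that needs correcting.

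**What to change.** 1. Reconcile Modeling approach with Limitations: either 10–12 of about 13 CBOs (77–92%) or 12–13 (92–100%).
2. Remove or qualify the near-population statements in Modeling approach and Limitations, and the small-sample statement in Power. If a coverage remark is kept, limit it to CBO-level sampling error when describing these two regions.
3. Rest the focus on effect estimates on the exploratory, estimation-oriented reasoning already in Limitations.
4. Commit to reporting every Aim 1 effect with a conventional 95% confidence interval that treats clinicians and schools as a sample. Show those intervals wherever effects are used to set the emphasis of the Aim 2 interview guide.

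The cost is a few sentences and routine output. No change to recruitment, measures or models is needed. The downside is that the stated precision becomes less favourable.

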##### Power

Our study is largely focused on estimating effects of an entire population rather than computing statistical significance or generalizing to a larger population and therefore potentially less susceptible to issues associated with calculating effect sizes in small samples [93, 94]. Nevertheless, we calculated power to detect effects in MLM by computing a “corrected sample size,” which adjusts the sample size by the correlation due to nesting [68, 95]. Assuming an ICC of .10 [96], our effective sample size to detect effects on clinician-level implementation outcomes with 35 clinicians would be *n* = 29. Thus, the proposed study has the sensitivity at power (1-*β*) = .80 (*α* = .05) to detect effects as small as *f*^2^ = .37.

### Aim 2: identification of preliminary implementation mechanisms

#### Procedures

Qualitative and mixed-methods inquiry is critical to mechanistic research [97]. To address Aim 2, visual summaries of Aim 1 quantitative, organizational data will be presented to all SBMH clinician participants to evaluate the ways in which alignment/misalignment of the CBO and school contexts influences their implementation of new practices. Because the objective is to describe the mechanisms through which IOA exerts its influence on SBMH clinicians, the perspectives of participants who directly experience both organizations (i.e., SBMH clinicians) are most critical. Individual semi-structured phone interviews, lasting approximately 45–60 min, will be conducted at a convenient time for clinicians and audio-recorded. Recordings will be transcribed prior to coding. The mixed methods design will be *sequential in structure* (quantitative data in Aim 1 collected prior to qualitative data in Aim 2); the functions are *explanation* and *expansion* (we will use qualitative data to provide depth and breadth of understanding to explain the mechanisms that explain the influence of IOA on implementation, i.e., QUAN➔QUAL), and the process is *connecting* (the qualitative dataset will build on the quantitative dataset) [35, 76, 98, 99]. Qualitative data in Aim 2 will explore the nuances of inter-organizational processes to understand mechanisms that affect implementation.

#### Qualitative interview protocol

We will develop a systematic, comprehensive semi-structured interview guide that examines underlying mechanisms through which inter-organizational processes facilitate or hinder EBP implementation. Feedback reports will be presented to participants for their respective school-CBO dyad and will include all of the organizational constructs measured in Aim 1 (i.e., OSC, ILS, ICS). Using these constructs as an overarching framework, we will generate questions that explore the inter-organizational implementation context as perceived by CBO clinicians and supervisors. Specifically, a series of questions will (1) request examples of how alignment/misalignment on each construct manifests in their work settings and (2) explore the mechanisms/processes through which degree of alignment/misalignment affects their ability to implement EBP. Questions will be carefully constructed to elicit clear information without assigning valence to performance. We also will ask questions about clinician embeddedness to gain a more nuanced understanding of the implications of clinician connections to and collaborations with the schools in which they work. Synthesis of this information will point to potential mechanisms through which IOA impacts successful implementation.

